### The Interventions

Trained physiotherapists conduct individualized training. They received training to operate the PerStBiRo system (Figure 1), and experienced it themselves to be able to determine the challenge for a participant and adjust the difficulty of the training. We use the same PerStBiRo system to train both, the PerTSBR and TSBR groups. Each group receiving 24 training sessions, twice a week for 12 weeks. Based on a recent systematic review (24) of PBBT paradigms, programs consist of low perturbation magnitudes as this is a more feasible program for each older adult, requiring longer training periods for significant improvement of reactive balance responses and reduction in fall incidence (24). Increasing the total PBBT volume increases the likelihood of its effectiveness (40). Since our PBBT program focuses on improving the trunk and arm balance recovery reactions in a sitting position, the program duration is as applied at lower magnitudes of PBBT during standing or walking, intensities that usually evoke fixed BoS strategies. Each session lasts for 20 min and includes three parts (Figure 2): stage (1) warm-up-−3 min of self-paced pedaling with the same bicycle resistance for both groups, corresponding to the training program level, without perturbations and cognitive tasks; stage (2) main exercises−15 min of perturbation training during hands-free stationary bicycling (PerTSBR). For details, see “Experimental group intervention,” with perturbations and “Control group intervention” without perturbations (TSBR) in combination with concurrent visual cognitive tasks for both groups. The graduated difficulty levels in bicycle resistance and the cognitive tasks are the same for both groups and determined according to the training program (details in Table 2); and stage (3) cool down-−2 min of self-paced pedaling without bicycle resistance, without perturbations and cognitive tasks. During stage 2 the participants are instructed to “ride the bicycle at your preferred pace and try to stabilize yourself. Try also to do your best in the cognitive tasks.” The cognitive dual-task exercises are presented using Microsoft Power Point on a TV screen 2.5 meters in front of the pedaling trainee's head. It includes tasks such as “Find the odd one out,” “Find a specific object in the picture,” and “Find the differences” between two pictures. For all tasks presented, the participant must state out loud where the object is, then have this checked by the trainer, and if the answer is correct, the next task is presented. During the training sessions trainees wear a loose safety harness that can arrest falling using the PerStBiRo system, but still allow comfortable pedaling and execution of balance recovery reactions with the upper body without the harness suspension. In both groups, each participants activities are documented in each session. See Figure 2 for a single-training session template and see detailed explanations in “Experimental intervention” and “Control intervention.”

**Figure 2 F2:**
[figure not shown]
Training session templates for PerTSBR and TSBR groups. Resistance= stationary bicycle resistance while pedaling, DT=dual tasks, Inter/Exter= internal/external, “floating” = a PerStBiRo–system's mode in which the moving platform and the stationary bicycle are unfixed and unstable; thus, it is subjected to tilting by the forces acting on it. Fixed mode is when the PerStBiRo is locked vertically, and it is used as a regular stationary bicycle. Motion capture mode refers to whether the motion capture system i.e., Microsoft Kinect^KM^ system works and monitors the trainee's movements, providing them with real-time external cues of their balance reactions. Levels refer to the level of the training program (details in Table 1).

### Experimental Group Intervention

The PerTSBR experimental group participants receives a combination of internal and external ML tilting perturbations during hands-free bicycling under dual-task conditions. This is provided by roll-angle (tilt) balance perturbations that aim to evoke trunk and arm balance recovery responses. The tilt pivot axis is formed by two ball bearings in the front and rear of the moving platform, crossing along the training bicycle and passing under the trainee's seat position (see Figure 3). The tilt pivot axis is lower than the trainee's CoM that is located in the pelvis above the bicycle seat. Therefore, when tilting the trainee's CoM aside rapidly, the trainee is forced to respond reactively with trunk and arm movements. The PerStBiRo system provides a maximum right and left perturbation tilt angle of 20° (each side) with maximum acceleration and deceleration of 30 m/s^2^ and maximum velocity of 30 m/s, which is usually that of a triangular motion profile for each perturbation (acceleration—deceleration). The computer program allows the therapist trainer to determine the perturbation training plan and control all balance exercise parameters: maximum acceleration/deceleration, maximum velocity, angle of perturbation, the number of right/left perturbation repetitions, and the delay time between each pair of consecutive perturbations.

In the second stage of the training session, i.e., the main training phase, has internal and unannounced external balance perturbation exercises in self-paced hands-free pedaling under dual-task conditions. Pedaling the PerStBiRo system in its unfixed and unstable “floating” mode causes self-induced perturbations similar to outdoor bicycling, and challenges proactive balance control. These internal perturbations are initiated from training level 5 (see Table 1). The programmed unannounced external perturbations are ranged from low to high controlled, unexpected machine-induced ML tilting perturbations, which evoke fast upper body reactive balance responses (i.e., trunk, hip, head, and arm movements). These perturbations can be programmed and delivered as a block or random (in onset, magnitude, and direction) type of training. During perturbation exercise, the PerStBiRo system provides trainees with real-time visual or sensorimotor external cues (cues are given from training level 3—see Table 1). (1) A visual cue for a beginner trainee is obtained by self-watching their balance performance in real-time on the television (TV) screen, like a mirror view. (2) For an advanced trainee, a sensorimotor cue is obtained by giving a real-time sensorimotor cue to the trainee's balance reaction following a perturbation. Once an unexpected balance perturbation is given, when an appropriate balance reaction is detected, the tilting platform (the perturbation) is stopped immediately, and the PerStBiRo system returns to its vertical position (details under “Perturbations”). This sensorimotor cue will lead to improve the trainee's internal sensorimotor feedback, therefore, to better implement motor learning of reactive balance control (41). In addition, concurrent visual cognitive tasks are displayed on the PerStBiRo system's TV screen.

The third stage of the training session, i.e., the cool-down part, consists of self-paced pedaling without bicycle resistance, and without cognitive tasks and external programmed perturbations. However, the fixed or “floating” PerStBiRo system mode remains as it was during a specific training, so the trainee may be exposed to self-induced internal perturbations.

The difficulty of the perturbation training level is adjusted according to the trainee abilities, starting from the lowest level at the first training session. If the trainee is able to recover from all perturbations during the session (i.e., one did not hold the bicycle handlebars or fall into harness system during the session and feels that they can be further challenged), a higher level of perturbations will be introduced in the next session. In case the trainee was not able to recover, the same level of perturbations is introduced again until the participant can successfully recover balance in the entire session. Assistance and support are provided for trainee who feel uncomfortable in the initial phase of the training. However, they are encouraged to perform exercises with no or minimal external support.

### The Perturbation Training Program and Progress

The training program (Table 2) consists of 22 potential training levels, which contain a gradual increase in difficulty in several exercise components with respect to motor learning, strength, endurance, and especially balance control:

1) The training always starts with hands-free cycling practice to avoid external support on the handlebars that significantly reduces the postural responses (42) and to calibrate the software to identify balance recovery responses.

2) The perturbation magnitude increases (i.e., increases displacement, velocity, and accelerations of the tilting translations).

3) The type of training shifts from the block PBBT method at the beginning, where the participant is aware of the direction of perturbation (right–left–right etc'), with a similar time interval between perturbation, thus these are an expected perturbation. Than announced random PBBT was introduced (random in onset, direction, and tilting magnitude of the perturbation). Varied practice in a random order results in better motor learning (43). This is supported by a recent study that found that, in retention and transfer tests, the results indicated higher values for random than for block perturbation training in healthy young participants (44).

4) The type of perturbation begins with external perturbations only when the simulator device is fixed and stable in the first sessions and changes to a combination of external and internal perturbations that are the unfixed and unstable surface which is affected by the forces exerted on the device while the trainee pedals in increasing intensity. Practicing in a variable and unstable environment is an advanced practice that contributes to improve skill acquisition (45).

5) The external cue type also changes from no cue at all to a visual cue that is like real-time viewing of a mirror on a TV screen during exercise and then changing to an external sensorimotor cue that leads to improving the intrinsic sensorimotor feedback. Once an unexpected balance perturbation is given, when an appropriate balance reaction is detected, the tilting perturbation is stopped, and the simulator system returns to its vertical position. This intrinsic task feedback provides the learner (trainee) with an implicit cue for successful balance response and provides the best possible motor learning implementation (41). In addition, at training levels 12, 16, and 20, no external cue is given in order to maximize the subject's upper body movements to improve their upper body range of motion (especially of the trunk).

6) The pedaling intensity.

7) The cognitive tasks difficulties also increase along the training process.

### Control Group Intervention

The control group (TSBR) receives 20 min of bicycle riding on the PerStBiRo system in its fixed mode along all of the training program (used as a regular stationary bicycle) without any internal or external perturbations (Figure 2), but dual-task training is provided. Pedaling intensity and cognitive tasks are the same as in the intervention group and follow the levels of difficulty that are reported in the training program (Table 2). This training method was chosen in order to match all other training components (i.e., session time and training period, and pedaling and cognitive demands), except for the balance challenge. Bicycle training programs have been shown to improve trainees' gait parameters (34) and increase muscle power and endurance (36), executive function (34, 35), and quality of life (33) in older adults. The control group not only receives balance, but also other important training components.

### Data Collection and Outcome Measures

First, by personal interview with one of the researchers at the enrollment session (T1), each participant completes demographic, medical history, and past fall questionnaires (see Table 1). Then they undergo two assessment sessions: first at entry of the study (baseline assessment, T1), and the second at the end of the 12-week intervention period (T2). To ensure data quality, two research assessors blinded to group allocation and the training process receive training regarding data collection from the principal investigator and perform all measurements.

### Primary Outcome Measures

Because this study deals with the ability to learn and generalize reactive balance responses that are acquired in a sitting position into a target context of fall risk factors and balance control performances in standing and walking situations, our primary outcome measures to evaluate the effect of PBBT during bicycle riding are derived from the ability to recover from unexpected external perturbations in the compensatory step execution tests during standing and walking. The best observational and kinematic measures to represent the reactive (compensatory) balance responses are: the single-step and multiple-step thresholds (observational parameters), and the first-step recovery initiation duration, first step duration, total balance recovery duration, and total CoM displacement (kinematic parameters) (14). All of these parameters have been previously found to be able to distinguish between younger and older adults (14) and fallers and non-fallers (15). The single-step threshold was previously shown to be an independent predictor of a future fall (16–21) and to reflect unsteadiness in reactive balance control among older adults with varying histories of falls (15). Moreover, excellent inter-observer reliability has been reported for single-step and multiple-step thresholds (ICC_2, 1_ = 0.978 and ICC_2, 1_ = 0.971, respectively; *p* < 0.001), and for first-step recovery initiation duration, first step duration, total balance recovery duration, and total CoM displacement (ICC_2, 1_=0.917, ICC_2, 1_=0.975, ICC_2, 1_=0.950, and ICC_2, 1_=0.918, respectively; *p* < 0.001) (14).

The compensatory step execution test examines reactive balance responses following unexpected platform translations. Perturbations are induced through a mechatronic device that provides controlled and unexpected AP and ML platform surface translations during standing and waking (46). For standing, participants are instructed to stand with feet placed together (heels and toes touching), resting arms naturally at their sides. For walking, participants are instructed to walk at their preferred treadmill walking speed with their hands free to swing (no handrails on the treadmill). Perturbations are synchronized to the initial contact phase of the gait cycle using the three-dimensional (3D) Vicon Motion System (Oxford, UK) and a code written in Mathlab for calculating the subject's own treadmill speed and step width. In standing as well as walking, participants are exposed to random of onset and random right/left/forward/backward unannounced platform translations that are increased systematically and controlled at ten perturbation magnitudes in increasing levels of difficulty. Four directional perturbations (right/left/forward/backward) occur in a random order at each level for a total of 40 perturbation trials (see Table 3 for perturbation details). During examination, participants wear a safety harness that prevents falls, but does not otherwise restrict their recovery balance movements. Falls during the assessment session are defined, as load cell sensors detect 30% or more of body weight suspended by the safety harness (48). Participants wear their own walking shoes and are instructed to react naturally to keep their balance and to prevent themselves from falling in response to perturbations. The increase in perturbation difficulty is adjusted by the examiner according to each subject's ability to recover. In case the subject should fall, grasp the examiner's hand, or ask to stop the test, the examination is stopped and will not continue to the next level. A seated rest break is given whenever needed. The data are analyzed observationally and kinematically for each trail.

**Table 3 T3:** Magnitude of the perturbation i.e., the parameters during the examination protocol of balance reactive response in standing.

**Perturbation size**	**Platform displacement (cm)**	**Perturbations velocity (m/s)**	**Perturbations acceleration (m/s^**2**^)**	**Perturbations random order**
Level 1	3	0.06	0.09	B, R, F, L
Level 2	4	0.06	0.18	B, F, R, L
Level 3	5	0.11	0.35	L, B, F, R
Level 4	6	0.16	0.52	F, R, B, L
Level 5	7	0.22	0.7	B, F, R, L
Level 6	8	0.33	1.1	B, F, L, R
Level 7	9	0.44	1.5	B, R, F, L
Level 8	12	0.66	2.0	B, F, R, L
Level 9	15	0.88	2.5	R, B, F, L
Level 10	18	1.20	3.0	B, R, L, F

*Perturbations will be induced through a mechatronic device that provides controlled and unexpected AP and ML platform translations during standing (47): four directional perturbations (right=R/left=L/forward=F/backward=B) in a random order in each of the 10 levels for a total of 40 perturbations*.

#### Observational Analysis

We verify single-step and multiple-step threshold levels for AP and ML directions following a loss of balance using a Vicon Motion System (Oxford, UK), allowing image pauses, slow motion, and running of the image back and forth. The single-step threshold level is defined as the minimum perturbation magnitude that consistently elicited a single compensatory step for at least two consecutive perturbation magnitudes. The multiple-step threshold is defined as the minimum perturbation magnitude that consistently elicited a sequence of recovery steps. During the analysis, we explore the step recovery strategies during all single-step and multiple-step trials during the whole protocol.

#### Kinematic Analysis

3D kinematic data are collected through optical motion capture (Vicon Motion Systems, Oxford, UK), providing kinematic analysis of a motion sequence. Sixteen infrared cameras cover the lab space, mounted at a height of 2.6 ± 0.2 meters and providing a capture volume of 5.5 × 1.2 × 2.0 m^3^ evenly scattered approximately four meters around the treadmill. The cameras operate and sample simultaneously, at a frequency of 200 Hz, the location of 39 reflective markers placed on anatomical landmarks of the body and another two on the moving platform. The markers are attached to a prepared whole-body flexible suit that comes in several sizes to properly fit each subject. Views from the 16 cameras are mapped onto a 3D coordinate system by the computer (Vicon Systems software) using an internal direct linear transformation algorithm. Perturbations that are followed by execution of a compensatory step (change in BoS) are digitized, transformed, and smoothed using a low-pass filter (Butterworth second-order forward and backward passes) with a cut-off frequency of 5 Hz. The Vicon system was shown to be valid and reliable. Overall trueness (systematic deviations) of a dynamic reference object was −0.23 ± 0.35 mm (−0.24 ± 0.36%) and overall uncertainty (random deviations) for dynamic measurements was 1.11 ± 0.94 mm (1.16 ± 0.99%). For lower body assessment (10 cameras, foot region) during walking, the mean trueness and uncertainty was 0.08 and 0.33 mm, respectively (47).

The following kinematic parameters are extracted: (1) the step initiation duration in milliseconds (ms) is calculated as the time from surface horizontal translation to step initiation, (2) first recovery stepping duration (ms) is calculated as the time from surface translation to foot-contact on the ground, (3) first compensatory step length is calculated as the Euclidian distance in centimeters (cm) that the ankle markers are displaced from step initiation to first step recovery, and (4) Margin of Stability (MoS), which is the distance between a velocity adjusted or “extrapolated” position of the CoM (XcoM) and the edge of an individual's BoS at any given instant in time. The MoS is directly related to the impulse (I) required to cause instability (49). When a participant takes extra steps to recover balance, i.e., a multiple-step reaction, the following parameters are determined: total balance recovery duration (ms), which is the time from surface translation to foot contact on the ground, completing multiple steps to recover balance; recovery step path length, which is the Euclidian distance in cm that the ankle markers are displaced from step initiation to foot contact on the ground, completing full balance recovery; and total CoM path displacement (cm), defined as the distance in cm of the CoM traveled from the initial point prior to stepping to the point where participants completed their full balance recovery. Using this method, Batcir et al. (14) found excellent inter-observer reliability for observational and kinematic analysis.

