### Statistical Analysis

PASW Statistics version 26.0 are used for statistical calculations. Baseline characteristics are compared using independent *t*-tests and Mann–Whitney *U*-tests for continuous and ordinal variables, respectively. Descriptive data analysis and tests for the assumptions of normality (Shapiro-Wilk's statistic) are followed by a two-way repeated measure analysis of variance (ANOVA) for within subjects (pre- vs. post-tests) and between groups (experimental vs. control groups). The primary outcome variables are the single-step and multiple-step thresholds, the first-step recovery initiation duration, first step duration, total balance recovery duration, and the MoS. These variables were previously found to be able to distinguish between younger and older adults (14) and between fallers and non-fallers (15). The single-step threshold was previously shown to be an independent predictor of a future fall (16–21) and to reflect unsteadiness in reactive balance control among older adults with varying histories of falls (15). The secondary laboratory outcome variables are foot contact time (voluntary stepping), and the ML CoP sway, as well as SDA parameters (Cd and Ds). All these parameters were previously found to reflect unsteadiness in balance control (13, 50, 55, 56, 58, 67, 68) related to falls (13, 55–58, 60), and also related to older adults who have bicycle riding habits (30). The other secondary outcome measures are the BBS, 6MWT, LLFDI, and FES-I. An intention to treat analysis is conducted by carrying the last obtained measurements forward for those participants who do not complete all aspects of the study. The significance level is *p* < 0.05.

The effect size (ES) (Hedge's g) between the two independent groups is calculated by dividing the difference between the means of each group by the pooled baseline standard deviation of both groups. Values between 0.2 and 0.49 are considered small, between 0.5 and 0.79 moderate, and 0.8 and higher is considered a large effect. In addition, for each outcome parameter, we explore whether a minimal detectable change has been reached. As data will be analyzed at the end of the study, there is no plan for interim analyses of primary and/or secondary variables.

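### The kinematic primary outcomes come only from trials with a step, which training is meant to reduce, so the arms may be compared on different perturbation magnitudes

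*Protocol article*

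**What the plan says.** The Statistical Analysis section names six primary variables. Two are observational: "The primary outcome variables are the single-step and multiple-step thresholds". The other four are kinematic: first-step initiation duration, first step duration, and then "total balance recovery duration, and the MoS". The Primary Outcome Measures section ends its kinematic list differently, with "first step duration, total balance recovery duration, and total CoM displacement (kinematic parameters", so the fourth measure is either total CoM displacement or MoS. The point below applies to both.

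The Kinematic Analysis section decides which trials supply these values: "Perturbations that are followed by execution of a compensatory step (change in BoS) are digitized, transformed, and smoothed". It narrows the set again for total recovery duration and total CoM displacement: "When a participant takes extra steps to recover balance, i.e., a multiple-step reaction, the following parameters are determined".

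For the thresholds, the Observational Analysis section states: "The single-step threshold level is defined as the minimum perturbation magnitude that consistently elicited a single compensatory step for at least two consecutive perturbation magnitudes". Table 3 has ten magnitudes. If the participant falls, grasps the examiner or asks to stop, "the examination is stopped and will not continue to the next level".

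The Introduction explains that hip, trunk and arm responses let a person recover without stepping and so raise the step threshold. It hypothesises that training transfers to standing and walking. The analysis is a two-way ANOVA, pre/post by group. No perturbation level or direction is named for the kinematic comparison.

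**The concern.** Whether a trial contains a step is observed after randomisation, and the intervention is designed to change it. If training works, trained participants stop stepping at the smaller perturbations, and those trials leave the kinematic data. What remains in the trained arm is a harder set of trials. For the multiple-step measures it may also come from a smaller and different set of people.

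A difference between arms in step timing, recovery duration, CoM displacement or MoS could then reflect the magnitudes analysed and not how well participants step. A real gain in threshold could appear as harm or as extra benefit on the kinematic measures, depending on how each varies with magnitude. Four of the six primary variables are exposed to this.

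**Working it through.** **Inputs from the protocol.** Sample Size Estimation: single-step threshold in standing 10.8 v 7.9 cm, SD 3.45 cm, 27 per group. Table 3: displacements 3, 4, 5, 6, 7, 8, 9, 12, 15 and 18 cm.

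**The plan's own figure.** With n = 2(1.96 + 0.84)²(SD/difference)², foot contact time (104 ms, SD 134 ms) gives 2 × 7.85 × 1.660 = 26.1, so 27 per group. The stated 27 is reproduced. This point changes no sample size.

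**Assumptions added.** Thresholds are normal, a participant steps at every level at or above the threshold, and all ten levels are given. The figures are for standing, per direction.

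**Step 1: how many levels give a step.** P(step at displacement m) = Φ((m − mean)/3.45).

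| m (cm) | 3 | 4 | 5 | 6 | 7 | 8 | 9 | 12 | 15 | 18 | Sum |
|---|---|---|---|---|---|---|---|---|---|---|---|
| mean 7.9 | 0.078 | 0.129 | 0.200 | 0.291 | 0.397 | 0.512 | 0.625 | 0.883 | 0.980 | 0.998 | 5.1 |
| mean 10.8 | 0.012 | 0.024 | 0.046 | 0.082 | 0.135 | 0.209 | 0.301 | 0.636 | 0.888 | 0.982 | 3.3 |

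Stepped levels fall from 5.1 to 3.3 of 10.

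**Step 2: which magnitudes are analysed.** Each participant's stepped displacements are averaged, then averaged over participants with at least one step: 12.8 cm at the control threshold and 14.7 cm at the trained threshold, a shift of 1.9 cm. If testing ended at 12 cm for everyone, the shift would be 1.0 cm, and participants with no stepped trial in that direction would be 12% v 36% (1 − 0.883 and 1 − 0.636).

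**Step 3: what the shift does.** Suppose there is no true kinematic effect, 27 per arm, one T2 value per participant averaged over stepped levels, and between-participant SD of 1. The spurious difference is slope × shift. The slope is an assumption, because the protocol gives none.

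| Slope (SD per cm, either sign) | Spurious difference, all levels | False positives, all levels | False positives, testing ends at 12 cm |
|---|---|---|---|
| 0 | 0 | about 5% | about 5% |
| 0.05 | 0.05 × 1.9 ≈ 0.10 SD | 6–7% | about 5% |
| 0.10 | 0.10 × 1.9 = 0.19 SD | 10–11% | 5–6% |

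Steeper slopes give more. For example, an assumed 20–30 ms per level with assumed SDs of 60 ms between and 40 ms within participants gives about 16–24%.

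**Step 4: the threshold's upper end.** A single-step threshold at level k needs a step at k and k + 1. With ten levels the largest scorable k is 9 (15 cm). A participant who first steps at level 10, never steps, or is stopped before a second stepped level has no defined value. Under the same normal model, P(threshold > 15 cm) = 1 − 0.888 = 11% at the trained mean and 1 − 0.980 = 2% at the control mean. This is a tail extrapolation from reported means and shows only that the gap could differ by arm.

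**The case against.** The best counter-argument is that the article does not say how up to 40 trials become one value per participant. Values could be taken at a matched level and direction, and a full analysis plan may say so. Matching would remove the shift in magnitude, so silence on level is not a decision to pool. That stands as far as it goes. But the restriction to stepped and multiple-step trials is written into the article itself, and even matched values are conditional on who steps.

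It is also fair that the size is assumption-led. The documents give neither a slope nor an SD for the compensatory-step kinematics, and with no slope the magnitude shift does no harm.

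A reader might infer three stronger things that the documents do not support:

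- **That all primary outcomes share this flaw.** They do not. The single-step and multiple-step thresholds are also primary, and fewer low-level steps show directly as a higher threshold. Their weakness is an unscored upper end, not selection of trials.
- **That the carry-forward rule puts T1 in place of an undefined threshold, so the best responders lose their gain.** The rule is written for participants who do not complete all aspects of the study. Someone who takes every perturbation without a qualifying step has completed the test. Losses of power calculated from that substitution therefore do not follow from the text.
- **That false positives are 16–24%.** That range needs the steep slopes and SDs assumed in the last example of the working.

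**Conclusion.** The concern holds for the four kinematic primary outcomes, most strongly for total recovery duration and total CoM displacement, which need a multiple-step trial. If training raises the threshold as the plan expects, the arms are compared on different magnitudes and partly on different participants. On the plan's own thresholds the shift is about 1.9 cm with all levels given (1.0 cm if testing ends at 12 cm), assuming normal thresholds and stepping at every level above the threshold.

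The direction and size of the resulting bias are not determined by the documents. False positives run from about 5% with no relation to magnitude to about 6–11% at 0.05–0.10 SD per cm with all levels given, and higher only under steeper assumed slopes.

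The threshold ceiling at level 9 is a real but smaller and separate gap: some participants have no defined value, and the article gives no rule for scoring them. The change is worth making before analysis, but the threshold comparison remains usable once scoring is fixed.

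**What to change.** 1. Compare each kinematic variable at matched perturbation level and direction. One way is a trial-level mixed model with arm, level, direction, T1 value and a random participant effect. State that the results are conditional on stepping (or on multiple stepping), and report by arm how many participants and trials contribute at each level. Matching removes the magnitude shift but not the selection of who steps, so the conditional label is needed. Re-ranking these outcomes as secondary is a design preference that the repair does not require.
2. Fix the threshold scoring. Place participants with no qualifying step by the end of the scale in a top category, treat those stopped early as censored at the last level passed, and do not replace either with T1. Analyse the threshold by a method that accepts ordered or censored values, adjusted for T1.

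The cost is analysis wording and modest programming. The article says the data are analysed trial by trial, so no new measurement is needed. The small downside is a model less simple to report than a two-way ANOVA.
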